### 2.3. Sample Size

To secure a representative sample of children in childcare, a random cluster sampling strategy will be used. In a meta-analysis exploring the effectiveness of 15 physical activity interventions targeting preschool-age children, Gordon and colleagues [29] reported that most studies had a small-to-moderate effect (Hedges *g* = 0.4) for change in young children’s total physical activity levels after participating in an intervention. If we convert this to f2, we can estimate this effect size to be approximately 0.12. Using the pwr package [30] within R version 3.6.0 [31], a minimum sample size of 99 children will be required (assuming 80% power and an experiment-wise alpha of 0.05). To account for a clustering effect, using an intra-cluster coefficient of 0.05, and an average cluster size of 16 children, the design effect is: 1 + 0.05 (16 − 1) = 1.75. Therefore, the sample size will be inflated to 175. Based on our recently conducted studies using accelerometry within the childcare environment [9], an anticipated loss to follow-up/accelerometer non-compliance rate of 20% is anticipated. To adjust for this, we aim to recruit 218 children.

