### 2.8. Analysis

All data will be entered, verified, and stored in our lab. Baseline characteristics of the children and the childcare centres will be summarized descriptively; participant characteristics for those who complete the study and those who drop out will be explored. All statistical analyses will be performed in R [31], using the lme4 [40] and lmerTest packages [41].

Implementation Log. Frequencies and percentage scores will be calculated to reflect adherence to policy statements and reasons that compliance was not attained will be reported descriptively.

Program Evaluation Survey and Interviews. Means and standard deviations of survey item ratings will be provided. Responses to open-ended program evaluation survey and interview questions will be analyzed using thematic content analysis [42] using QSR NVivo.

Physical Activity. Children’s physical activity data will be analyzed using a series of linear mixed effects models for each of the three outcome variables (i.e., TPA, MVPA, and sedentary time). Group (experimental versus control) and time (baseline, mid-intervention, post-intervention, and six-months post-intervention) will be modelled as a fixed effect, and will be evaluated using *t*-tests, with a Satterthwaite approximation determining degrees of freedom. Descriptive survey data will be analyzed using frequencies, *t*-tests, and chi-square tests.

Childcare Providers’ Self-Efficacy. Descriptive statistics will be reported to indicate changes in childcare providers’ self-efficacy specific to implementing physical activity in childcare. Classical test theory will be used to assess internal consistency of the scales, exploratory factor analysis will be used to assess the factorial validity of the measured constructs, and item response theory will be used to explore the item and scale characteristics of the measurements used to assess the two polytomous constructs in this study (i.e., task and barrier self-efficacy). Factor analysis and classical test theory analyses will be undertaken within the psych package [43] and the ltm package [44] will be used for the item response theory analyses.

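### The sample size claims an experiment-wise alpha of 0.05, but the analysis tests three outcomes in separate models with no lead outcome, testing order or adjustment, so the claimed control is not delivered as written

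*Protocol article*

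**What the plan says.** Section 2.3 of the Protocol article fixes the error rate for the sample size: "assuming 80% power and an experiment-wise alpha of 0.05". The effect size is a "small-to-moderate effect (Hedges *g* = 0.4) for change in young children’s total physical activity levels", so TPA is the only outcome that enters the calculation.

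Section 2.8, under Physical Activity, says that the children's data will be analysed "using a series of linear mixed effects models for each of the three outcome variables (i.e., TPA, MVPA, and sedentary time"). Group and the four occasions are fixed effects, tested by t-tests with Satterthwaite degrees of freedom. No group-by-time interaction is written out. No outcome is ranked above the others, no order of testing is given, and no adjustment is mentioned. Nor does the section say that the tests are unadjusted.

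Three other places bear on the point:

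- The abstract and section 1 make feasibility the primary aim; the abstract lists activity and sedentary time as secondary.
- The Hypothesis section predicts changes in all three outcomes between baseline and post-intervention, treats follow-up separately, and makes no prediction for mid-intervention.
- The specific objectives in section 1 cover MVPA, TPA and sedentary time as matters on which the policy may prove effective.

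**The concern.** An experiment-wise alpha is a statement about the whole set of tests: the probability of at least one false positive among them is held at 5%. That is true if a single test carries the claim, if the tests are taken in a fixed order, or if they are adjusted. Section 2.8 describes none of these. The article therefore asserts a property that its own printed analysis does not have, which goes beyond a detail left out.

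In practice, a positive result on any one of the three outcomes could be reported as effectiveness at 5%, although only TPA was sized. Agreement between outcomes could also mislead. If the outcomes are expressed per hour of wear, sedentary time is 60 minutes minus TPA, so a significant sedentary result repeats the TPA result and does not corroborate it.

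**Working it through.** **1. The plan's own sample size.** Inputs from section 2.3: "we can estimate this effect size to be approximately 0.12" (f2, taken here as stated), 80% power, alpha 0.05, "a minimum sample size of 99 children will be required", "the design effect is: 1 + 0.05 (16 − 1) = 1.75", 20% loss, and "we aim to recruit 218 children". The numerator degrees of freedom u are not stated.

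The power function is the noncentral F with noncentrality f2 × (u + v + 1), solved for the denominator degrees of freedom v:

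| u | alpha | v |
|---|---|---|
| 1 | 0.05 | 65.4 |
| 2 | 0.05 | 80.4 |
| 3 | 0.05 | 90.9 |
| 4 | 0.05 | 99.3 |
| 5 | 0.05 | 106.6 |
| 1 | 0.01 (= 0.05/5) | 98.7 |

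The stated 99 is matched by u = 4 at alpha 0.05 if v is read as the number of children (the full N would be 99.3 + 4 + 1 = 104.3). It is matched equally well by u = 1 at alpha 0.01. The sample size therefore does not show whether alpha was divided.

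The later steps are 99 × 1.75 = 173.25 (stated 175) and 175 / 0.8 = 218.75 (stated 218). Both are close to the stated figures.

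**2. One group test per outcome.** This is the least that section 2.8 implies: three tests, each at 0.05.

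- Independent tests: 1 − 0.95³ = 0.143. For two-sided tests on jointly normal statistics, correlation can only lower this, so 14% is a ceiling.
- Three outcomes with a common correlation (simulation, 400,000 draws of normal statistics, cut-off 1.96): 13.5% at correlation 0.3, 12.6% at 0.5, 11.0% at 0.7, 8.4% at 0.9, 7.4% at 0.95.
- TPA and sedentary time as exact complements, leaving two distinct tests: 9.8% at TPA-MVPA correlation 0, 9.1% at 0.5, 8.3% at 0.7, 7.0% at 0.9.

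**3. Three group-by-occasion contrasts per outcome.** This is an assumption, since no interaction is written out. Four occasions give three post-baseline contrasts, so there would be 3 × 3 = 9 tests.

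- Independent tests: 1 − 0.95⁹ = 0.370.
- Correlation 0.5 between occasions (assumed): 31.7% at outcome correlation 0.3, falling to 17.9% at 0.95.
- The same, with TPA and sedentary time as exact complements (six distinct contrasts): 23.5% at TPA-MVPA correlation 0, 20.3% at 0.7, 17.2% at 0.9.

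The correlations are assumptions, because the article gives none. Every scenario computed lies above 5%.

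**4. What an adjustment would cost in children.** On the u = 4 route with v read as N, Bonferroni over three outcomes (alpha 0.05/3) gives 129; 129 × 1.75 = 226; 226 / 0.8 = 283, against 218 stated. A single carrying contrast or a fixed order needs no increase for multiplicity.

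**The case against.** The strongest reply is that the article condenses a fuller plan. Multiplicity procedures are commonly left to that plan, and nothing printed rules one out. The stated 99 is even compatible with a divided alpha. This stands in part: it cannot be said that no adjustment exists, and the sample size proves nothing either way. It does not remove the point, because the article itself makes the experiment-wise claim and then sets out an analysis that lacks it.

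A second reply is that the emphasis is already there: the Hypothesis section points to post-intervention, and section 2.3 sizes on TPA. That is fair for the occasion. Three outcomes still remain at that occasion, and nothing says which of them carries the 0.05.

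A third reply is that the stakes are small. The outcomes are secondary, the trial is a pilot, and section 1 foresees a larger effectiveness study. This stands and lowers the severity. Section 3 does connect the findings to provincial standards, but only as a long-term potential and only if the policy proves both effective and appropriate to implement.

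A reader might infer that the actual error rate is 14-37%. The documents do not support that. Both ends require independent, unadjusted tests, whereas MVPA is part of TPA and sedentary time is close to its complement. The upper end also needs nine contrasts from an interaction that section 2.8 does not specify, and coefficients for time alone do not test the intervention.

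The mirror relation has a limit of its own. It is exact only per hour of wear (or at fixed wear time); section 2.8 does not state the unit, and with raw minutes and varying wear time it is only approximate.

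**Conclusion.** The point holds in a limited form. The error control stated in section 2.3 is not delivered by the analysis in section 2.8 as written. Without adjustment and with one group test per outcome, the experiment-wise error is about 7-10% if sedentary time mirrors TPA, and at most 14%. If group-by-occasion contrasts are also tested, it is roughly 17-32% under the assumed correlations, with 37% as the value for nine independent tests. The size within these ranges depends on correlations, on the unit of the outcomes and on the number of contrasts, none of which the article settles. Severity is low, because these are secondary outcomes of a feasibility pilot.

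**What to change.** In sections 2.3 and 2.8, name the between-arm difference in TPA at post-intervention as the one contrast that carries the 0.05. It uses the outcome on which the study was sized and the occasion in the hypothesis. Report MVPA, sedentary time and the other occasions as supportive estimates with unadjusted 95% confidence intervals, and note that sedentary time largely mirrors TPA.

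If the team does not want a lead outcome, delete the term experiment-wise and state that 0.05 applies to each test. A fixed testing order or a stated adjustment would also resolve the contradiction; Bonferroni at the same power would raise the recruitment target, as shown in the working.

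The preferred change costs one or two sentences and no additional children. Its downside is that results on MVPA or sedentary time could not by themselves support a claim of effectiveness.

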### 2.4. Recruitment and Randomization

To secure an adequate sample size, this study will be conducted in eight randomly selected childcare centres (i.e., the clusters) chosen from an online listing of 55 eligible licensed childcare centres in London, Canada. Since it is necessary to implement the policy at the centre-level to groups of children, the childcare centres (i.e., the clusters) rather than the individual participants, will be randomly allocated by the project coordinator to either implement the physical activity policy (experimental; *n* = 4), or maintain their daily programming (control; *n* = 4) for the eight-week intervention period (at which time the policy will no longer be enforced).

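### The design effect assumes 16 children per cluster, but eight centres with 175 analysed children means about 22 per centre, so the effective sample size is about 86, not the 99 required.

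*Protocol article*

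**What the plan says.** Protocol article, section 2.3 (Sample Size), builds the target in four steps:

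- Effect size: a Hedges g of 0.4 is converted to f², and "we can estimate this effect size to be approximately 0.12".
- Unclustered size: "a minimum sample size of 99 children will be required (assuming 80% power and an experiment-wise alpha of 0.05").
- Clustering: "using an intra-cluster coefficient of 0.05, and an average cluster size of 16 children", so that "the design effect is: 1 + 0.05 (16 − 1) = 1.75". It continues: "Therefore, the sample size will be inflated to 175".
- Loss: "an anticipated loss to follow-up/accelerometer non-compliance rate of 20% is anticipated". The result is: "To adjust for this, we aim to recruit 218 children".

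Section 2.4 (Recruitment and Randomization) sets the number of clusters: "this study will be conducted in eight randomly selected childcare centres". It identifies the centres as the clusters twice, and allocates them four to the policy and four to usual programming.

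**The concern.** A design effect of the form 1 + ICC × (m − 1) is only valid if m is the number of children per cluster that the design will actually have. Here three figures are fixed independently: clusters (8), children per cluster (16) and total (175 analysed, 218 recruited). The third should be the product of the first two, and it is not.

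The direction of the error matters. The number of centres is fixed, so inflating the total adds children to the same centres. This raises m, and with it the design effect. Using 16 understates the inflation, and the plan falls short of its own minimum. What is at stake is the 80% power claim for the children's activity outcomes, and the design effect that a planner of the larger trial mentioned in the Background might carry forward.

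**Working it through.** **Inputs.** From section 2.3: unclustered N = 99, ICC = 0.05, m = 16, loss = 20%, f² = 0.12. From section 2.4: k = 8 centres, randomised 4 v 4. Equal centre sizes are assumed throughout.

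**Step 1. Reproduce the plan's figures.**
- Design effect = 1 + 0.05 × (16 − 1) = 1.75.
- 99 × 1.75 = 173.25. The stated 175 is within rounding (100 × 1.75 = 175 exactly).
- 175 / 0.8 = 218.75, stated as 218.

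The arithmetic reproduces from its own inputs. The problem is the input m = 16.

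**Step 2. Test m = 16 against eight centres.**
- 8 × 16 = 128 children.
- At 16 per centre, 175 children need 175/16 = 10.9 centres, and 218 need 218/16 = 13.6.
- In eight centres, 175 analysed is 175/8 = 21.9 per centre, and 218 recruited is 218/8 = 27.25 per centre.

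**Step 3. Recompute at the cluster size the design implies.** Effective N = N / [1 + 0.05 × (N/8 − 1)].

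| Scenario | m | Design effect | Effective N | Shortfall v 99 |
|---|---|---|---|---|
| 175 analysed | 21.9 | 1 + 0.05 × 20.875 = 2.04 | 175/2.044 = 85.6 | 14% |
| 218 analysed (no loss) | 27.25 | 1 + 0.05 × 26.25 = 2.31 | 218/2.3125 = 94.3 | 5% |

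The analysed size, about 22, is the relevant one. The target is missed in both rows.

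**Step 4. ICC at which 175 analysed would suffice.** (175/99 − 1) / (21.875 − 1) = 0.768/20.875 = 0.037, below the plan's 0.05.

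**Step 5. What reaching 99 in eight centres would take.** Solve 8m / (0.95 + 0.05m) = 99: m = 99 × 0.95 / (8 − 99 × 0.05) = 94.05/3.05 = 30.8. That is 8 × 30.8 ≈ 247 analysed and 247/0.8 ≈ 309 recruited.

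**Step 6. Cost in power.** Section 2.3 names the R package but not the numerator df (u), so a range is needed. Noncentral F, f² = 0.12, alpha 0.05, noncentrality 0.12 × N, denominator df N − u − 1:

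| u (assumed) | Power at N = 99 | Power at N = 85.6 |
|---|---|---|
| 1 | 93% | 89% |
| 2 | 87% | 81% |
| 3 | 82% | 75% |
| 4 | 77% | 70% |

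The loss due to the cluster size is about 4 to 7 points in each row.

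As an illustration on centre-level df: f² = 0.12 in a two-group comparison implies d = 2 × √0.12 = 0.69. With 4 v 4 centres there are 6 df, and the noncentrality is d × √(effective N / 4).
- Effective N = 99: 0.693 × √24.75 = 3.45, power 82%.
- Effective N = 85.6: 0.693 × √21.4 = 3.21, power 76%.

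**The case against.** **The 16 may be a classroom size, or net of loss.** Neither reading works. Section 2.4 defines the clusters as centres and randomises centres, so a classroom-based design effect would leave out the randomised level. If 16 were the analysed number, recruitment would be 16/0.8 = 20 per centre, or 160 in total, not 218.

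**This is a feasibility pilot.** This stands, and it limits the severity. The abstract lists children's activity among the secondary objectives. Feasibility is assessed by logs, surveys and interviews that are analysed descriptively and thematically. The primary conclusion does not rest on this calculation. Still, section 2.3 makes an explicit 80% power claim, so its inputs should agree with each other.

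**The article condenses a longer protocol.** Nothing is said to be missing here. The figures printed in two adjacent sections conflict.

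A reader might also infer more than the article supports:

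- *That power in the plan's own test falls to 70%.* That figure needs u = 4, which the article does not state. At u = 4, N = 99 gives only about 77% before any correction of the cluster size; at u = 1 or 2, power stays above 80% even at 85.6.
- *That the true ICC must be higher.* The Discussion says that centres influence activity more than age, sex or ethnicity. It gives no ICC, so it does not show that 0.05 is wrong.
- *That unequal centre sizes make the shortfall larger by a known amount.* Table 1 admits centres from eight consents, so sizes may vary, but the article gives no size distribution. Any coefficient of variation would be a reviewer's assumption.

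**Conclusion.** The inconsistency is real: 16 per cluster, eight clusters and 175 analysed children cannot all hold, and nothing in the article reconciles them. At the plan's own ICC the design effect is 2.04 rather than 1.75. The effective sample size is about 86, at best 94, against a stated minimum of 99.

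The size is moderate: 14% short (5% with no loss) and about 4 to 7 points of power. The shortfall itself rests only on printed figures and equal centre sizes. The power figures also need an assumed numerator df. The 82% to 76% illustration uses d = 0.69, which is implied by f² = 0.12 but is not a planning effect that the article states; it states g = 0.4.

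This should be fixed. It is not a defect that invalidates the trial, because it concerns a secondary objective and changes no design feature, data collection or analysis.

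**What to change.** Keep eight centres and 218 children, and rewrite the clustering step of section 2.3 as follows:

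- Derive the cluster size from the design: about 22 analysed children per centre.
- State a design effect of 2.04 at ICC 0.05 and an effective sample size of about 86.
- State the numerator df used for the 99, and replace the 80% claim with the power, or the detectable effect, that results on centre-level degrees of freedom.
- Optionally, add a labelled sensitivity row for a higher ICC or unequal centre sizes, marked as an assumption.

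Adding children is an inefficient remedy, since about 309 recruits would be needed in the same eight centres, and a feasibility pilot does not call for it.

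Cost: rewording of one section. The stated power becomes slightly less favourable.

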### 2.4. Recruitment and Randomization

To secure an adequate sample size, this study will be conducted in eight randomly selected childcare centres (i.e., the clusters) chosen from an online listing of 55 eligible licensed childcare centres in London, Canada. Since it is necessary to implement the policy at the centre-level to groups of children, the childcare centres (i.e., the clusters) rather than the individual participants, will be randomly allocated by the project coordinator to either implement the physical activity policy (experimental; *n* = 4), or maintain their daily programming (control; *n* = 4) for the eight-week intervention period (at which time the policy will no longer be enforced).

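### Eight centres cannot give the stated 80% power for g = 0.4 at the plan's own ICC of 0.05, however many children are enrolled

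*Protocol article*

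**What the plan says.** Section 2.3 (Sample Size) takes a meta-analytic effect of Hedges g = 0.4 for change in total physical activity. It then states: "If we convert this to f2, we can estimate this effect size to be approximately 0.12". From this it concludes that "a minimum sample size of 99 children will be required", "assuming 80% power and an experiment-wise alpha of 0.05". Clustering is handled "using an intra-cluster coefficient of 0.05, and an average cluster size of 16 children", so that "the design effect is: 1 + 0.05 (16 − 1) = 1.75". The total becomes 175, and 218 after allowing for 20% loss or non-compliance.

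Section 2.4 (Recruitment and Randomization) turns this into a number of clusters: "To secure an adequate sample size, this study will be conducted in eight randomly selected childcare centres", four per arm. Section 2.8 (Analysis) tests group and time effects on total activity (TPA), MVPA and sedentary time in linear mixed models, using t-tests with Satterthwaite degrees of freedom.

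**The concern.** A design effect corrects the number of children for clustering. It does not show that the number of randomised units is large enough. Two limits depend on the count of centres and are absent from the calculation:

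- **Variance floor.** Adding children within a centre reduces only the within-centre part of the variance. The between-centre part is fixed by the number of centres.
- **Degrees of freedom.** A centre-level contrast with eight centres has 8 − 2 = 6 degrees of freedom, whereas a calculation on 99 children assumes over 90.

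The trial has effectiveness objectives on activity and sedentary time (end of section 1), and the Discussion links a favourable result to institutional policies and provincial standards. A reader told that the power is 80% could take a null result as evidence that the policy does not work, when the design had about a one-in-three chance of detecting the cited effect.

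**Working it through.** **Inputs from the protocol.** g = 0.4, f2 = 0.12, 80% power, alpha 0.05, ICC 0.05, 16 children per centre, 99, 175 and 218 children (section 2.3); k = 4 centres per arm (section 2.4); Satterthwaite t-tests (section 2.8). **Assumption:** two-sided testing, since the sides are not stated.

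**1. The plan's own chain.** 99 × 1.75 = 173.3 (stated 175; 100 × 1.75 = 175 exactly). 175 / 0.80 = 218.75 (stated 218). The chain reproduces to within rounding. At 16 per centre, however, eight centres hold 8 × 16 = 128 children. The 175 analysed need 175 / 8 = 21.9 per centre.

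**2. Variance with k centres per arm and m children per centre, SD = 1.**

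Var(difference) = (2/k) × [ICC + (1 − ICC)/m]

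- Unlimited children: (2/4) × 0.05 = 0.025, so SE = 0.158 and noncentrality = 0.4 / 0.158 = 2.53.
- m = 21.9: design effect = 1 + 0.05 × (21.875 − 1) = 2.044; SE = √(4 × 2.044 / 175) = 0.216; noncentrality = 0.4 / 0.216 = 1.85.

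**3. Power for g = 0.4**, from the noncentral t on 6 df (critical value 2.45) and from the normal approximation (1.96).

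| Children per centre | t, 6 df | Normal |
|---|---|---|
| 16 | 30.3% | 40.2% |
| 21.9 (175 in all) | 34.5% | 45.7% |
| 100 | 49.5% | 64.0% |
| Unlimited | 56.3% | 71.6% |

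A shortcut confirms the ceiling. Unclustered, g = 0.4 needs about 98 to 99 children per arm. Multiplied by ICC 0.05, this is about 4.9, which exceeds the 4 centres per arm, so no finite cluster size reaches 80% even with the normal critical value.

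**4. Detectable effect at 80% power on 6 df** (noncentrality required 3.367).

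- 175 children: 3.367 × 0.216 = 0.73 SD.
- Unlimited children: 3.367 × 0.158 = 0.53 SD.

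**5. Cost of the degrees of freedom alone.** The noncentrality needed for 80% power is 2.830 on 97 df and 3.367 on 6 df. (3.367 / 2.830)² = 1.42, so 42% more information is required. A design with noncentrality 2.83 has 66% power on 6 df.

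**6. At the effect implied by f2 = 0.12.** For two equal groups d = 2√f2 = 2√0.12 = 0.69. At 175 analysed, power is 76% on 6 df, against 89% at child-level df. With unlimited children it is 95%.

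**7. Sensitivity to the ICC (g = 0.4, 6 df).**

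| ICC | Power, unlimited children | Power, 175 analysed |
|---|---|---|
| 0.01 | over 99% | 52% |
| 0.02 | 91% | 46% |
| 0.03 | 78% | 41% |
| 0.05 | 56% | 34.5% |
| 0.10 | 33% | 25% |

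**8. Baseline adjustment.** For a ceiling of 80%, the remaining centre variance must be at most 2 × (0.4 / 3.367)² = 0.0282. That means removing 1 − 0.0282/0.05 = 44% of it. If baseline and follow-up correlate at 0.7 or 0.8 (assumed values, applied at both centre and child level), power at 175 analysed is about 58% or 73%.

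**The case against.** **The stated 80% belongs to f2 = 0.12, not to g = 0.4.** This is right as far as it goes. At 0.69 SD eight centres meet no ceiling below 80%: power is 76% at 175 analysed and reaches 80% at about 219 analysed. The fall to about 35% therefore combines a faulty conversion with too few centres. But the plan presents f2 = 0.12 as its translation of g = 0.4. Once that conversion is corrected, the limit set by eight centres remains. Even on the plan's figure, power at 175 is below 80%.

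**The analysis uses baseline.** The hypothesis concerns change, and the mixed models include the baseline measurement. Stable centre differences cancel in a change contrast, so the true floor may be lower than 0.025. This stands as a qualification. Section 2.3 claims no such gain and gives no correlation, however, and at 175 children even a correlation of 0.8 falls short of 80%.

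**The ICC is uncertain.** The ceiling does pass 80% at an ICC just below 0.03. But 0.05 is the plan's own value, and at 175 children even 0.01 gives only 52%.

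**It is a pilot with feasibility as its primary aim.** True, and a good reason to keep eight centres. It limits how much the shortfall matters. It does not make the power and adequacy statements correct.

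**Conclusion.** The concern holds. For g = 0.4 with ICC 0.05, four centres per arm and a two-sided 5% test, power is at most 56% on 6 df (72% with a normal critical value) and about 35% at the planned 175 analysed. The detectable effect is 0.73 SD at 175 children and cannot go below 0.53 SD. On the plan's f2 of 0.12 the shortfall is smaller, at 76% against the stated 80%.

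These figures treat ICC 0.05 as applying to the outcome on which g is standardised, as the plan's own design effect does, and take no credit for baseline adjustment. With a one-sided 5% test on 6 df the ceiling for g = 0.4 is 72%, so the conclusion does not depend on the number of sides under the planned t-tests.

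**What to change.** Keep the eight centres. In sections 2.3 and 2.4, replace the statements on 80% power and adequate sample size with a calculation for 4 v 4 centres on a t distribution with 6 df. For example: with 8 centres, 175 analysed children and ICC 0.05, the trial can detect about 0.73 SD with 80% power, and power for g = 0.4 is about 35%. If credit for baseline is wanted, state the assumed correlation and its source, and show the power across a range of correlations and ICCs.

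It would also be sensible, though the correction does not depend on it, to present the activity and sedentary-time results chiefly as estimates with confidence intervals. That would touch the wording of the effectiveness objectives and section 2.8 as well.

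The core change is a rewording of two sections. It needs no more centres or children; the price is a less favourable power figure.
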